**Abstract**

**Introduction:** HIV/AIDS is the leading cause of mortality among women aged 15 – 44 years. In Africa is there a huge gender disparity in the acquisition of HIV. African women aged 15 – 24 are twice as likely to be infected with HIV than their male counterparts. However, in Cameroon, adolescent girls are five times more likely to be infected with HIV than boys of the same age. Evidence suggests that risks taken during transactional and commercial sexual relationships account for this gender inequality. Recent studies demonstrate that a key driver of a woman’s engagement in risky sexual behaviours is to cope with negative income shocks (e.g., agricultural and climatic shocks, illness or death of family members), suggesting that economic shocks are a substantial piece of the HIV puzzle in Africa. This study is the first to estimate the effectiveness of a formal coping strategy, health insurance, to protect women from economic shocks to prevent STIs and HIV.

**Methods and Analysis**: This study is a stratified cluster randomised controlled superiority trial with two parallel groups. 1,508 unmarried girls and young women engaging in transactional (753) and commercial (755) sex have been recruited onto a baseline study in Yaoundé, Cameroon. Participants are randomised into treatment (receiving health insurance for them and their economic dependents) and control (receiving nothing) groups using participatory randomisation. A target of a 1:1 allocation was stratified by those who engage in commercial or transactional sex. Midline data will be collected at 6 months and 12 months after randomisation.

**Ethics and Dissemination:** This trial has been prospectively registered with the ISRCTN Registry. We obtained ethical approval from Cameroon National Ethics Committee and the UCL ethics committee before data collection. The findings of the trial will be published in peer-reviewed journals irrespective of the final results.

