**Methods: Participants, interventions and outcomes**

**Study setting {9}**

The trial is being conducted in Yaoundé, Cameroon. Cameroon was chosen because it has one of the highest gender disparity in HIV globally, adolescent girls aged 15–19 are five times more likely to be infected with HIV than their male counterparts [2% versus 0.4%] (16).

The implementing partner is John Hopkins Cameroon Program (JHCP), an NGO experienced in conducting research for John Hopkins University. Recruitment of participants using respondent-driven sampling (RDS) is hosted by two partner Community-based organisations (CBOs), Horizon Femmes (HF) and RENATA. HF and RENATA were chosen because of their extensive experience and excellent ongoing work in STI and HIV prevention with the target population. Both organisations were recommended by the implementing partner JHCP.

All women and girls engaging in commercial and transactional sex who have received a recruitment coupon and meet the eligibility criteria can participate. Recruitment of participants into the study began in June 2021. The randomisation of participants began in October 2021.

After negotiations with several health insurance and care providers in Cameroon and on the advice of local partners (JHCP, HF and RENATA), GMC assurances and Cité Verte Hospital were the chosen health insurance and healthcare providers. GMC assurances was chosen as they offered the best value insurance package. The choice of hospital was based on the quality of care, availability of medication on site and the positive culture and experience in providing care to stigmatised and vulnerable groups.

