**Outcomes {12}**

**Overview**

There are several methods of data collection. The socio-economic and biobehavioural surveys occur over three time periods: baseline, 6 months after baseline (midline), and 12 months after baseline (endline). The SMS survey occurs fortnightly, commencing just after the completion of the baseline for 52 weeks. The surveys are administered in both French and English, depending on the participant's language preference.

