**Secondary outcome measures**

Secondary outcomes include:

1. Physical health of participants measured using % of participants with good health, % of participants with a chronic illness other than Hepatitis B, the average number of chronic illnesses, % of participants who were sick in the last 30 days, % who sought treatment from a qualified health worker if sick in the last 30 days, % of participants with abnormal levels of Gardnerella vaginalis (GV), Mobiluncus, Candida and streptococcal in the vagina (only at endline)

2. Physical health of economic dependents measured using % of economic dependents with good health, % of economic dependents with a chronic illness, the average number of chronic illnesses per economic dependent, % economic dependents who were sick in the last 30 days, % economic dependent who were sick during sex act with last client, % economic dependents who were sick during sex act with the penultimate client, % of children with good health

3. Beliefs regarding control over own health measured using % who believe that nothing can be done to prevent illness, % who believe that being in good health is a matter of luck

4. Poverty measured using total expenditures, asset index, income from sex work, amount of savings, % who have Informal shock-coping strategies, average amount of transfers received and sent, % who have a debt, amount of the debt, food insecurity

5. Education/training measured using % school dropout, new enrolment in schools, % who are undertaking professional training

6. Other occupation measured using transitions out of sex work, % who have other occupation, share of sex work income in total income

7. Risky sexual behaviours measured using % of condom use with last and penultimate client using a double list experiment and the colourbox method, a newly indirect elicitation method developed by the team members, number of clients per week, type of sex acts performed with last client, self-reported risk preferences with sex (out of 10 scale), % of were pregnant the last 6 months, % who performed both transactional sex and sex work

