**Data collection and management**

**Plans for assessment and collection of outcomes {18a}**

There are several methods of data collection. The socio-economic and biobehavioural surveys occur over three time periods: baseline, 6 months after baseline (midline), and 12 months after baseline (endline). The surveys are administered in both French and English, depending on the participant's language preference. The primary outcomes of the study are STI acquisition and HIV status will be measured via the biobehavioural and socioeconomic survey conducted at baseline, midline and endline. At baseline, we will test for syphilis, chlamydia, gonorrhoea and trichomoniasis. For financial reasons, we will only collect HIV and the two most prevalent STIs at the midline. At endline we will test for all the STIs tested at baseline (syphilis, chlamydia, gonorrhoea and trichomoniasis). In addition, to allow for a better understanding of the participants' non-sexually transmitted infections status, the levels of GV, Mobiluncus, Candida and streptococcal in the vagina will also be tested. Testing the levels of these bacteria and fungi is a secondary outcome. It is important as sexual activity is associated with an increased risk of imbalance of these bacteria or fungi in the vagina which may lead to infections such as Bacterial vaginosis (BV), Candidiasis and Group B Strep infection. Evidence suggests that there is a positive relationship between a person having these infections and an STI and HIV(17). Biological tests (blood tests and vaginal swabs) to test for STIs, HIV and non-sexually transmitted bacteria and fungi are conducted at the same time as the socioeconomic survey.

Other secondary outcomes are measured via the biobehavioural and socioeconomic survey conducted at baseline, midline and endline. Additional measures for secondary outcomes will also be captured in the fortnightly SMS survey. The survey questionnaire will include sociodemographic questions, income, health status, demand for healthcare, economic shocks, STI prevention, risky sexual behaviours, violence, personality traits and preferences.

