**Trial status**

Protocol version: Final version as of 10 March 2023

Recruitment dates: The date of first enrolment was 2 June 2021 and participants are currently being followed-up.

Enrolment status: No longer recruiting.

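### The pregnancy measure counts any pregnancy in the last 6 months, so midline includes many conceived before allocation; this costs precision without biasing the percentage-point difference

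*Protocol*

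**What the plan says.** Item 7 of the Protocol's Secondary outcome measures opens with "Risky sexual behaviours measured using % of condom use with last and penultimate client" and later lists the percentage who "of were pregnant the last 6 months". Section {18a} says of the remaining secondary outcomes: "Other secondary outcomes are measured via the biobehavioural and socioeconomic survey conducted at baseline, midline and endline". So pregnancy is asked three times with the same look-back.

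The timing of the visits has two anchors. The Overview under Outcomes {12} and section {18a} place midline and endline 6 and 12 months after baseline. The Abstract says "Midline data will be collected at 6 months and 12 months after randomisation". The choice matters because the dates differ: Trial status states "The date of first enrolment was 2 June 2021", Study setting {9} states "The randomisation of participants began in October 2021", and Intervention description {11a} starts the insurance on 15 November 2021.

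Eligibility criteria {10} do not exclude women who are pregnant at entry. Section {20a} compares the allocated groups by ordinary least squares, accounting for baseline or attrition differences. No section limits the pregnancy measure to new pregnancies.

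**The concern.** As a marker of risky sex, the informative event is a conception after the woman knows whether she is insured. The definition counts being pregnant, not becoming pregnant. A woman who conceived 5 months before the start and delivered 4 months after it is positive at midline, although allocation cannot have affected that conception. A woman who conceived 2 months before the start and delivered at month 7 is positive at both visits for the same reason.

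The Protocol separates new from existing events elsewhere. It treats STIs at baseline so that the cohort starts free of them, counts only active syphilis at follow-up, and specifies new school enrolment. The pregnancy item has no such rule. At stake is the ability to see a real fall in unprotected sex through this marker, mainly at midline.

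**Working it through.** The Protocol gives no figure for pregnancy, so there is nothing to reproduce.

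**Inputs.** From the Protocol: a 6-month look-back; visits at 6 and 12 months; 568 control and 579 treatment participants (Sample size {14}). Assumed, because the documents do not give them: a constant conception rate, pregnancy duration D months, and a lag of L months before the woman knows she is pregnant. Time 0 is the start of follow-up.

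**Shares conceived before the start.**
- Midline counts conceptions between −D and 6−L. Share before 0 = D / (D + 6 − L).
- Endline counts conceptions between 6−D and 12−L. Share before 0 = max(0, D − 6) / (D + 6 − L).
- Positive at both visits: conceived between 6−D and 6−L. Share = (D − L) / (D + 6 − L).

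| D | L | Midline, before start | Endline, before start | Endline positives also positive at midline |
|---|---|---|---|---|
| 4 | 0 | 4/10 = 40% | 0% | 40% |
| 4 | 1 | 4/9 = 44% | 0% | 33% |
| 5 | 0 | 5/11 = 45% | 0% | 45% |
| 5 | 1 | 5/10 = 50% | 0% | 40% |
| 7 | 0 | 7/13 = 54% | 1/13 = 8% | 54% |
| 9 | 0 | 9/15 = 60% | 3/15 = 20% | 60% |
| 9 | 1 | 9/14 = 64% | 3/14 = 21% | 57% |
| 9 | 1.5 | 9/13.5 = 67% | 3/13.5 = 22% | 56% |

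A simulation at D = 9, L = 0 gave 60.0%, 20.0% and 59.9%. If half of pregnancies end at 2.5 months and half at 9 (mean 5.75, L = 0), the shares are 5.75/11.75 = 49% at midline and (0.5 × 3)/11.75 = 13% at endline. So the endline share does not vanish when a short mean hides some full-term pregnancies.

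**Effect of a gap before insurance.** If the window opens g months before insurance starts (L = 0), the midline share conceived before insurance is (D + g)/(D + 6). For g = 1.5 it is 10.5/15 = 70% at D = 9 and 6.5/11 = 59% at D = 5. If visits run from baseline, a woman enrolled on 2 June 2021 reaches 6 months on 2 December 2021, about two and a half weeks after insurance began. Individual dates are not given, so the average gap is unknown.

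**Effect on the comparison.** Take D = 9, L = 0, an assumed 1.5% conceptions per month, and a true 30% fall.
- Midline as defined: 1.5 × 15 = 22.5% against 1.5 × (9 + 6 × 0.7) = 19.8%, a difference of 2.7 points.
- Midline, new conceptions only: 1.5 × 6 = 9.0% against 6.3%, also 2.7 points.
- Endline as defined: 22.5% against 1.5 × (3 + 12 × 0.7) = 17.1%, a difference of 5.4 points.
- New conceptions over 12 months: 1.5 × 12 = 18.0% against 12.6%, also 5.4 points.

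The differences agree. The relative reductions do not: 2.7/22.5 = 12% at midline and 5.4/22.5 = 24% at endline, against 30% for new conceptions. A simulation in which pregnant women cannot conceive again gives the same picture: 2.2 against 2.3 points at midline and 4.4 against 4.5 at endline.

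**Power** (568 and 579, two-sided 5%, D = 9):

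| Conceptions per month (assumed) | Midline as defined | Midline, new only | Endline as defined | New over 12 months |
|---|---|---|---|---|
| 1.0% | 14% | 28% | 44% | 52% |
| 1.5% | 20% | 41% | 63% | 72% |
| 2.0% | 27% | 52% | 79% | 86% |

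**The case against.** The strongest reply is that nothing is diluted on the planned scale. Least squares on a yes/no outcome estimates a difference in percentage points, and pregnancies conceived before allocation add the same amount to each arm in expectation. This stands. A reader might infer that a true 30% fall would be reported as 12%, or that the estimate is biased towards no effect. The first holds only for a relative reduction, which section {20a} does not specify. The second does not hold for the planned difference. What remains is added variance, heavy at midline and modest at endline.

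A reader might also infer that one pregnancy is counted twice. Two wave-specific percentages may share a pregnancy without error. It becomes double counting only if the waves are pooled or events are summed, and no section says so.

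The item is also a garbled phrase, the questionnaire is not shown, and it may ask about new pregnancies or record dates. That is a fair limit. But the written wording describes being pregnant, and it is the only definition in the document.

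Finally, item 7 holds more direct measures, such as condom use and number of clients, and the power statement concerns STIs and HIV only. That stands and sets the weight of the point.

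**Conclusion.** The definition as written admits conceptions that allocation cannot affect: about 40% to 67% of midline positives and 0% to 22% of endline positives over the durations and lags tried. It is safe to call the midline share substantial. The documents do not support calling it a majority, because that needs a mean duration above about 6 months without a recognition lag (4.5 months with a lag of 1.5), and no duration is given. If visits are timed from baseline, the share conceived before insurance is higher.

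The cost is precision and a shrunken relative effect, not bias: roughly half the power at midline and some 7 to 9 points of power over 12 months in the illustration. These figures rest on assumed conception rates, a constant rate and full-term pregnancies. This is a minor issue in one component of one secondary outcome, and no primary conclusion depends on it.

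**What to change.** Define the outcome as at least one pregnancy that began after randomisation, each pregnancy counted once, cumulative to endline. Date the start from gestation, last period or delivery date asked at endline. Where the start cannot be dated, exclude or adjust for women who reported a pregnancy at baseline; this uses only pre-allocation information, so it does not disturb the randomised comparison. Do not interpret the midline percentage as an effect on new conceptions. State whether visits are timed from baseline or from randomisation.

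The cost is one dating question for women who report a pregnancy, plus a sentence of analysis wording. On the stated schedule midline has passed, so the question can no longer be added there. At 10 March 2023 participants were still being followed up, but the Protocol does not say how many endline visits remained; for the others, existing dates or the baseline adjustment must serve. The downside is slightly fewer counted events and some recall error in the start date. The baseline item will also miss pregnancies not yet recognised and those conceived between baseline and randomisation.

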8. Violence measured using % who experienced violence (threats, physical, sexual, emotional/psychological) the last time they had sex with a client, % who experienced violence the penultimate time they had sex with a client, % who experienced violence by a current partner in the last 6 months, % who experienced violence by a sugar daddy in the last 6 months, % who experienced violence by another sex worker in the last 6 months, % who experienced violence by an occasional client in the last 6 months, % who experienced violence by a regular client in the last 6 months, % who experienced violence by police in the last 6 months, % who experienced violence by their pimp in the last 6 months, % who experienced violence by hostel owners in the last 12 months

9. Stress measured using perceived stress scale 4 (PSS-4)

10. Self-efficacy measured by participants' ability to deal with issues in different domains of their life

11. Loneliness measured using UCLA 3 Item Loneliness scale

12. Discrimination measured using Everyday Discrimination Scale (Short Version)

13. Stigma measured using % who have at least one of their family or friends aware that the participant has having paid sex, % who expect discrimination by family if HIV positive, % who consider themselves as a sex worker

14. HIV and STI knowledge measured using knowledge of participants regarding ways HIV can be transmitted, average knowledge of STI symptoms

15. Social networks measured using the number of friends in sex work, the number of peers who provide financial support

16. Mental health measured using % that are depressed using PHQ-9 scale, % who are happy, % satisfied with life, % with good self-esteem

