**Sample size {14}**

The baseline study has recruited 1,508 unmarried girls and young women engaging in transactional (753) and commercial (755) sex in Yaoundé, Cameroon. Currently, 1,147 participants have been randomised via participatory randomisation, 568 participants allocated to the control arm and 579 allocated to the treatment arm. To maximise statistical power, STI-positive participants receive free treatment at baseline to start the trial with an STI-free cohort. Participants will also receive free treatment at midline to allow for the possibility to observe more than one STI per participant over the trial period. Free treatment will also be provided at endline for ethical reasons. Assuming that 20% of participants will get at least one STI over the trial period, this sample size is sufficient to show a decrease of 30% (6 percentage points) in the incidence of any STI in the treatment group assuming 80% power and a significance level of 5%. To conduct analysis separately among the sub-samples of those engaging in commercial and transactional sex, the MDE is a ~40% reduction (8.3 percentage points) in STI incidence. Assuming an HIV incidence of 4% over the trial period, the sample size would allow the detection of a decrease of 65% in HIV incidence (2.6 percentage points).

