**Assignment of interventions: allocation**

**Sequence generation {16a}**

Randomisation is conducted at the individual level using a participatory approach with a target of a 1:1 ratio to treatment or control group stratified by engagement in commercial or transactional sex. Formative research, conducted before randomisation, found that participatory randomisation was the preferred method of randomisation by the target population. Participatory randomisation was deemed fairer and more transparent than computer-based randomisation.

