**Statistical methods**

**Statistical methods for primary and secondary outcomes {20a}**

All statistical analyses will be conducted using STATA. Descriptive statistics will first be used to summarise participant characteristics between the study groups. To investigate the effect of health insurance on primary and secondary outcomes, the analysis will use an intention-to-treat (ITT) approach where participants will be analysed in their allocated randomised study group. If there are non-compliers, i.e., participants and economic dependents who do not use the health insurance product when sick, we will also estimate the local average treatment effect (LATE). To investigate the effect of health insurance on primary and secondary outcomes, baseline characteristics will be compared for the treatment and control groups and determine whether there is differential attrition between the two groups. Outcomes for the treatment versus the control group will then be compared accounting for any baseline or attrition differences using ordinary least squared. The analysis will be conducted for all women and then separately for women engaging in transactional and commercial sex separately. A causal mediation analysis will be conducted to assess how much of the effect of health insurance on STI and HIV acquisition operates through risky sexual behaviours.

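### The only listed depression outcome is the percentage depressed on the PHQ-9; adding the total score would recover about a third to two thirds of the information at little cost

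*Protocol*

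**What the plan says.** The Protocol's section on secondary outcome measures lists 16 items. The last begins "Mental health measured using % that are depressed using PHQ-9 scale" and goes on to three further percentages, for happiness, life satisfaction and self-esteem. The PHQ-9 is therefore administered as a scale but enters the outcome list only as a percentage. The cut-off is not named, and neither a mean nor a total score is listed. Stress (item 9), loneliness (item 11) and discrimination (item 12) are separate constructs, so item 16 is the only place where depression is measured.

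For the comparison, Statistical methods {20a} states: "Outcomes for the treatment versus the control group will then be compared accounting for any baseline or attrition differences using ordinary least squared". This covers primary and secondary outcomes, by intention to treat. Sample size {14} reports that "1,147 participants have been randomised via participatory randomisation, 568 participants allocated to the control arm and 579 allocated to the treatment arm", and gives power for STI and HIV only. Plans for assessment and collection of outcomes {18a} says that the other secondary outcomes are surveyed at baseline, midline and endline. Trial status says that recruitment has closed.

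**The concern.** Cutting a score into depressed or not depressed ignores every change in symptoms that does not cross the threshold. A woman who moves well down the scale but stays on the same side of the cut counts as unchanged. The estimate is then less precise than one from the score itself, and a real improvement or worsening is more likely to be reported as no difference. The sample cannot be enlarged to compensate. The planned ordinary least squares model would take the total score as it stands, and the protocol gives no clinical or other reason for preferring the cut alone.

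**Working it through.** **The plan's own figure.** There is none to reproduce: the protocol states no power or detectable effect for the PHQ-9 or any other secondary outcome.

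**Inputs from the Protocol.** 568 control and 579 treatment (Sample size {14}); 5% significance and 80% power (same section; two-sided assumed).

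**Inputs assumed, because the Protocol does not give them.** A normal PHQ-9 score with equal SD in both arms; control prevalence of depression from 5% to 50%; an effect set so that the total score has exactly 80% power; no baseline adjustment; full follow-up.

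**Step 1: effect that the score detects with 80% power.**
- sqrt(1/568 + 1/579) = 0.0591
- d = (1.960 + 0.842) × 0.0591 = 0.165 SD

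**Step 2: the same effect expressed as a percentage.** With control prevalence p, the cut is c = Φ⁻¹(1 − p) and the treated prevalence is q = 1 − Φ(c + d). Power for two proportions is Φ[(p − q − 1.96 × s0) / s1], where s0 is the pooled and s1 the unpooled standard error.

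Example at p = 20%: c = 0.842; q = 1 − Φ(1.007) = 15.7%; s0 and s1 are both 0.0226; power = Φ[(0.0431 − 0.0443) / 0.0226] = Φ(−0.06) = 48%.

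**Step 3: information kept by the cut.** For small effects and a normal score this is φ(c)² / [p(1 − p)]. At p = 20%: 0.280² / 0.16 = 49%.

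| Control depressed | Treated depressed | Power of the percentage (score = 80%) | Information kept |
|---|---|---|---|
| 5% | 3.5% | 24% | 22% |
| 10% | 7.4% | 35% | 34% |
| 20% | 15.7% | 48% | 49% |
| 30% | 24.5% | 55% | 58% |
| 40% | 33.8% | 59% | 62% |
| 50% | 43.4% | 61% | 64% |

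To regain 80% power for this effect, the percentage would need about 3,670, 2,480, 2,070 or 1,810 women in total at 10%, 20%, 30% or 50% depressed, against 1,147 randomised.

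**Step 4: sensitivity to the shape of the score.** A skewed 0-27 score (negative binomial, means 4 to 10, assumed cut at 10, effect again set for 80% power on the mean) gives 34% to 63% power for the percentage, at control prevalences of 5% to 47%.

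**Step 5: sensitivity to the effect size.** Normal score, 568 v 579:

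| Effect | Score | 10% depressed | 20% | 30% | 40% | 50% |
|---|---|---|---|---|---|---|
| 0.25 SD | 99% | 63% | 81% | 88% | 91% | 92% |
| 0.30 SD | >99% | 78% | 92% | 96% | 98% | 98% |

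The loss of information stays, but it matters less for the test once the effect is large.

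**The case against.** A percentage depressed is a legitimate outcome that policy readers understand, and least squares handles a binary outcome as a risk difference. Item 16 is also consistent within itself, since all four of its measures are percentages. The cut-off and any supporting analysis of the score are details that an analysis plan, not shown here, often supplies. All of this stands, and it is why the percentage should stay. It does not remove the point, because the protocol itself names the metric: an analysis plan that follows it would compare only the percentage.

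Several stronger readings are tempting, and the documents do not support them.
- A reader might infer that the cut throws away most of the score. Under a normal score that is so only at about 20% depressed or below; at 30-50% the cut keeps 58-64% of the information. The protocol gives no prevalence.
- A reader might take 35-61% as the trial's power for depression. It is conditional on an effect chosen to give the score 80% power, and the protocol targets no PHQ-9 effect.
- A reader might infer that depression is a main outcome, or that the trial's stated power is wrong. It is one of four measures in the last of 16 secondary items, the sample size covers STI and HIV only, and the primary conclusions are untouched.
- A reader might infer that the neighbouring scales will be analysed as scores. Items 9, 11 and 12 name an instrument and give no metric, so they show nothing either way.

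Timing also matters. The protocol version is dated 10 March 2023, after insurance cover ended on 14 November 2022, and Blinding {17a} leaves researchers unblinded during conduct. Replacing a pre-specified measure that late would need justification. This weighs against substitution, much less against addition.

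**Conclusion.** The point holds as an inefficiency, not an error. The trial's only listed depression outcome is a cut scale, with no total score beside it and no reason given. For an effect of 0.165 SD, which the score would detect with 80% power, the percentage has about 35-61% power at 10-50% depressed and 24% at 5%. That is a loss of about one third to two thirds of the information over the 10-50% range. For effects near 0.30 SD the practical gap is small unless depression is uncommon. All of these sizes rest on the assumed prevalence, score shape and effect. The direction does not: the percentage was weaker than the score in every scenario tried.

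**What to change.** In item 16, add the PHQ-9 total score as a between-arm comparison, using the least squares model already planned and adjusting for the baseline PHQ-9 total if it was collected ({18a} indicates that secondary outcomes are surveyed at baseline). Keep the percentage depressed as already listed and name its cut-off. Record the addition as a dated change made before any unblinded analysis.

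The cost is one more secondary comparison and a dated amendment. No new data are needed, because the total is the sum of the PHQ-9 items that the percentage already requires. Policy readers keep the percentage.
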